The primary outcomes will be activity limitation and quality-adjusted life years. Activity limitation will be measured with the Lower Extremity Functional Scale [26] which involves the participant rating the degree of difficulty in performing 20 functional activities on a 5-point scale ranging from 0 ('extreme difficulty or unable to perform activity') to 4 ('no difficulty'). The scale has excellent test-retest reliability (intraclass correlation coefficient (ICC) 0.94), is sensitive to change and has high internal consistency and construct and concurrent validity for people with ankle fracture [27]. Quality-adjusted life years will be measured by the Assessment of Quality of Life instrument, which is designed to measure health-related quality of life and to be the descriptive system for a multi-attribute utility instrument. The Assessment of Quality of Life measures five dimensions: illness, independent living, social relationships, physical senses and psychological well-being, all of which have been shown to be orthogonal and unidimensional [28]. The Assessment of Quality of Life has been shown to be internally consistent (alpha = 0.81) and has a comparative fit index of 0.90 [28], and is reliable and more sensitive to health status than other multi-attribute utility instruments [29].

Secondary outcomes will be the number of days to pain-free walking, the number of days to return to full pre-fracture work, return to pre-fracture work and leisure activities, ankle dorsiflexion range of motion, pain, walking speed, physical activity, and global perceived effect of treatment (Table 1).

**Table 1 T1:** Secondary outcome measures assessed at baseline, 1, 3 and 6 months, unless otherwise stated.

Outcome	Description of assessment
Number of days to pain-free walking	Participants will be given a calendar to mark the first day they can walk pain-free for 10 meters to calculate the number of days elapsed from the day of randomisation to pain-free walking [5].
Number of days to return to full pre- fracture work	Participants who worked prior to fracture will be given a calendar to mark the first day they return to their pre-fracture work to calculate the number of days elapsed from the day of randomisation to return to full pre-fracture work.
Return to pre-fracture work and leisure	Self-reported percentage return to full pre-fracture work and leisure, where 0% is 'not participating at all' and 100% is 'returned to full level'.

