### Economic evaluation

The economic evaluation will consist of cost-effectiveness and cost-utility analyses. Costs will be measured in terms of direct costs to the health system and out-of-pocket costs to the participants over a 6-month period, and collected in a questionnaire at the 1, 3 and 6 month follow-up period. From an economic perspective, costs are measured by resource use. This allows the identification of the opportunity cost of resources used, that is, what could have been achieved had those resources been allocated to the best alternative use. In this trial the costs of the interventions and any out-of-pocket costs incurred by participants will be identified, measured and valued. Table 2 indicates the type of resources which will be captured, the sources of data, and proposed methods of valuation.

**Table 2 T2:** Assessment of resource use.

Type of resource	Method of assessment	Method of valuation
Physiotherapists' time	Physiotherapists' report	Salary rates plus on-costs for physiotherapists using published prices
Equipment	Questionnaires at 1, 3, 6 months	Manufacturer's price (depreciated over 3 years)
Medication, visits to general practitioners and other health professionals, hospitalisation, visits to emergency department	Questionnaires at 1, 3, 6 months	Published prices (e.g. Pharmaceutical Benefits Scheme and Medicare Benefits Schedule reimbursement) and/or actual costs to participants
Visits to community services or alternative or complementary health practitioners	Questionnaires at 1, 3, 6 months	Actual costs to participants

The cost-effectiveness analysis will use the Lower Extremity Functional Scale [26] as a measure of effectiveness. The cost-utility analysis will use the Assessment of Quality of Life instrument as a measure of utility.

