The primary conclusions about effectiveness of rehabilitation will be based on between-group comparisons of activity limitation and quality of life at 3 months. The primary conclusions about whether fracture severity and age and gender influence the effectiveness of intervention will be based on the interactions between these factors and effects of rehabilitation for activity limitation and quality of life at 3 months.

The economic evaluation will examine differences between participants in the *Rehabilitation *and *Advice *groups in terms of costs incurred and changes in perceived activity limitation (cost-effectiveness analysis) or utility gained (cost-utility analysis). The incremental cost-effectiveness (utility) ratio (ICER) will be calculated as: ICER = (*C_R _*- *C_A_*)/(*U_R _*- *U_A_*), where C is average cost, U is the average effectiveness or utility score, and subscripts R and A denote the *Rehabilitation *and *Advice *arms. The *Rehabilitation *program can be said to be cost-effective relative to *Advice *about exercise if it (a) produces less activity limitation or greater utility at a lower cost or (b) the cost per activity limitation avoided or per quality-adjusted life years gained (i.e. the incremental cost-effectiveness (utility) ratio) is less than some threshold value (e.g. $50,000). Bias-corrected bootstrapped estimates (1,000 replications) will be used to test for the difference in mean costs and to obtain 95% confidence intervals for between-group differences in mean costs. Between-group differences in utilisation will be tested using Fisher's exact test. Sensitivity analyses will be undertaken to explore the robustness and validity of the results. Both costs and outcomes will be varied in line with results from similar studies reported in the literature and the upper and lower limits of estimates from this trial.

To establish the predictors of outcome after ankle fracture, univariate linear regression will be used to examine the relationship between seven baseline variables (fracture severity, pain, ankle range of motion, mobility, depression, anxiety and stress, and pain catastrophising) and activity limitation at 1-month and 6 months after removal of immobilisation. A multivariate linear prediction model will be developed using methods described by Harrell [32].

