### Sample size

A sample of 76 participants (38 per group) would provide an 80% probability of detecting a difference between the group means of 10 points on the 80-point Lower Extremity Functional Scale (assuming a SD of 15 points, based on data from our recently completed trials [5,6]). This sample size will also provide 80% probability of detecting a difference between the group means of 2.75 points on the 45-point Assessment of Quality of Life scale (assuming a SD of 4 points, based on data from our recently completed trial [5]). Effects smaller than these are unlikely to be considered clinically worthwhile. In our calculations we assumed an alpha of 0.05, and we allowed for 5% loss to follow-up. We conservatively ignored the extra precision conferred by the longitudinal design.

In order to power the trial for analyses of the interactions with fracture severity and age/gender of participants we need to inflate the sample size by a factor of 2 + *k *+ 1/*k*, where *k *is the sub-group ratio. We anticipate the sub-group ratio for both *severe*: *less severe *fracture and *women aged over 50*: *others *is ~1:2 (based on our recently completed studies [5,6]). Thus, a sample of 72 × 4.5 = 342 participants (171 per group) will be recruited.

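### The cost-utility ratio is defined on a utility score but read as cost per QALY, and the second primary outcome appears in three incompatible forms

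*Protocol article*

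**What the plan says.** **The ratio (Statistical analysis, economic paragraph).** The ICER is the difference in average cost divided by the difference in U, where "U is the average effectiveness or utility score". One legend serves two analyses: cost-effectiveness on the Lower Extremity Functional Scale (LEFS) and cost-utility on the Assessment of Quality of Life (AQoL). The decision rule that follows takes the cost "per quality-adjusted life years gained (i.e. the incremental cost-effectiveness (utility) ratio"), and Rehabilitation counts as cost-effective if this "is less than some threshold value (e.g. $50,000").

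**The utility measure (Economic evaluation).** "The cost-utility analysis will use the Assessment of Quality of Life instrument as a measure of utility". The same section sets a 6-month horizon for costs. No section says that utility is accumulated over that horizon.

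**The primary outcome.**
- Outcome assessment: "The primary outcomes will be activity limitation and quality-adjusted life years", and "Quality-adjusted life years will be measured by the Assessment of Quality of Life instrument". The Abstract and the Discussion also name QALYs as primary.
- Sample size: the powered difference is "2.75 points on the 45-point Assessment of Quality of Life scale", with an assumed SD of 4 and no time point.
- Statistical analysis: the mixed model lists quality of life, measured at each visit, and does not list QALYs. The primary conclusions on effectiveness rest on "between-group comparisons of activity limitation and quality of life at 3 months".

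**The concern.** A utility score describes one moment. A QALY is that score multiplied by time and summed over the follow-up, here at most half a year. A ratio with score units in the denominator therefore cannot be judged against a threshold in cost per QALY. Cost-effectiveness is part of the primary aim, so an analyst who follows the printed formula could put a headline conclusion on the wrong side of the threshold.

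The primary-outcome wording mixes the same two quantities. If QALYs are primary, the outcome has no effect size, no SD and no place in the stated effectiveness model, and it does not carry the primary conclusion. If the AQoL score at 3 months is primary, the outcome is misnamed in the Abstract, Outcome assessment and Discussion. Which quantity is primary should not be left to be settled once results are known.

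**Working it through.** **1. The plan's own sample size.** Inputs from Sample size: LEFS difference 10, SD 15; AQoL difference 2.75, SD 4; alpha 0.05 (taken as two-sided); power 80%; 5% loss. Formula: n per group = 2(1.96 + 0.84)² × (SD/difference)².
- LEFS: 36 per group; 36/0.95 gives 38, so 76 in total, as stated.
- AQoL score: 34 per group; 34/0.95 gives 36. With 38 × 0.95 evaluable per group, power is about 83%, so the stated 80% is met.
- Interaction factor with k = 1/2: 2 + 0.5 + 2 = 4.5, and 76 × 4.5 = 342, as stated. (The printed multiplicand of 72 would give 324; 342 follows from 76.)

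The figures reproduce, but for a difference in scale points. The documents give no effect size or SD on the QALY scale, so no sample size for QALYs can be derived.

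**2. From utility to QALYs.** Visits are at 0, 1, 3 and 6 months. Trapezoid weights in years:
- baseline: 0.5 × 1/12 = 0.0417
- 1 month: 0.5 × (1/12 + 2/12) = 0.125
- 3 months: 0.5 × (2/12 + 3/12) = 0.2083
- 6 months: 0.5 × 3/12 = 0.125

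The QALY difference is the weighted sum of the between-group utility differences. True cost per QALY divided by the printed ratio equals the U difference divided by the QALY difference. A value above 1 means that the printed ratio understates cost per QALY.

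**3. Results for assumed time courses** (d is a difference on a 0–1 utility scale).

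| Difference at 0, 1, 3, 6 months | QALYs gained | Factor, U at 3 months | Factor, U at 6 months |
|---|---|---|---|
| 0, d, d, d | 0.458d | 2.18 | 2.18 |
| 0, d, d, 0 | 0.333d | 3.0 | no difference left |
| linear, reaching d at 6 months | 0.25d | 2.0 | 4.0 |
| 0, 0.06, 0.03, 0.01 | 0.015 | 2.0 | 0.67 |

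The last row is 0.06 × 0.125 + 0.03 × 0.2083 + 0.01 × 0.125 = 0.0075 + 0.00625 + 0.00125 = 0.015. Against a 6-month score difference of 0.01, the printed ratio overstates cost per QALY 0.015/0.01 = 1.5-fold.

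**4. Effect on the threshold.** In the first row, $50,000 per unit of score corresponds to 50,000/0.4583 = $109,091 per QALY. Illustration with an assumed cost difference of $500 and d = 0.02: the score ratio is 500/0.02 = $25,000, while cost per QALY is 500/(0.02 × 0.4583) = $54,545. The two fall on opposite sides of $50,000.

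**5. If U were the raw 45-point score.** With the same assumed $500 and the powered difference of 2.75 points, the ratio is 500/2.75 = $182 per point, which has no relation to a per-QALY threshold.

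**The case against.** The best defence is that the legend for U is loose shorthand shared by two analyses. The decision rule states the intended unit, cost per QALY, and the derivation of QALYs from utilities is a detail that a condensed article may leave to a full protocol or analysis plan. This has weight: silence on the derivation would be no finding. The article is not silent, however. It prints a score-based denominator and equates the resulting ratio with cost per QALY. The three forms of the primary outcome are also printed side by side, and the shorthand explanation does not reconcile them.

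Two further defences are that $50,000 is only an example and that sensitivity analyses are planned. The first is true, but the mismatch of units arises at any per-QALY threshold. The second does not help, because those analyses vary the values of costs and outcomes, not the unit of the denominator.

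A reader might infer that the printed ratio always understates cost per QALY, and by at least twofold. The documents do not support that: they name no visit for U, and a fading effect read at 6 months reverses the direction. Nor does the extreme case of a difference present only at 3 months, with U taken at that visit (1/0.2083 = 4.8-fold), describe what the plan would do. The same profile gives a zero denominator at 6 months, and 0.333/0.2083 = 1.6-fold if U is the mean of the three follow-ups. A reader might also infer that the sample size was set for 3 months, but the Sample size section names no visit; the 3-month point comes only from Statistical analysis.

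**Conclusion.** The point stands as a mismatch of units and a contradiction in a primary outcome. As written, the cost-utility ratio is not a cost per QALY and should not be compared with a per-QALY threshold. No single error factor can be attached to the plan. Under equal baselines and a constant difference at all three follow-ups, cost per QALY is understated about 2.2-fold; other plausible time courses and visits run from a 1.5-fold overstatement to a 4-fold understatement. These figures assume a 0–1 utility scale and linear change between visits. If the raw scale score were used, no comparison would be possible.

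The second primary outcome is named as one quantity, powered as another, and concluded on at a single visit that cannot yield a QALY. The total of 342 is not called into question for the AQoL score. What is unsupported is any claim that the trial was sized for QALYs.

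**What to change.** 1. In the cost-utility ratio, define U as mean QALYs per participant over 6 months: the area under the AQoL utility curve through baseline, 1, 3 and 6 months, with the between-group difference adjusted for baseline utility. Keep a score as U only in the LEFS cost-effectiveness ratio, and attach the per-QALY threshold only to the cost-utility ratio.
2. Reconcile the name of the second primary outcome with its powering and its primary conclusion. The simplest way is to state that the second primary effectiveness outcome is the AQoL score at 3 months and that 6-month QALYs are the outcome of the cost-utility analysis. The alternative is to keep QALYs as primary, which would require an effect size and SD on that scale and a 6-month primary conclusion.
3. Record the change as a dated amendment before results are seen.

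No new data are needed, since outcomes are scheduled at all four times; the analysis effort is small. It is nevertheless more than an edit of wording: recruitment began in December 2010, so clarifying a primary outcome has to be documented openly.

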The prediction of outcome after ankle fracture is relatively imprecise. We have previously shown that out of eight variables, pain and dorsiflexion range of motion soon after the period of immobilisation were the only independent predictors of outcome, but explained only 9 to 12% of the variance in activity limitation in the short- to medium-term [21]. Other variables (e.g. psychological factors) may be better predictors of outcome after ankle fracture. It has been shown that psychological variables (including pain catastrophising and depression) appear to be important predictors of outcome in people with other musculoskeletal conditions [22]. This issue has not been examined after ankle fracture.

The primary aims of the trial to be conducted are, therefore, to determine (a) the effectiveness and cost-effectiveness of rehabilitation, compared to simple advice and (b) if effects of rehabilitation are influenced by fracture severity or by the age and gender of participants. A secondary aim is to identify predictors of outcome after ankle fracture.

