### Outcome assessment

Outcomes will be assessed at baseline and 1, 3 and 6 months later. Outcome data will be obtained from all randomised participants, in so far as this is possible, regardless of compliance with the trial protocol. Outcome measurements will be made by an assessor blinded to allocation. The participants, as well as physiotherapists and investigators involved in the trial, will be asked to avoid giving information that could reveal participant's allocation to the blinded assessor. After each assessment the assessor will be asked if he or she was blinded to allocation and will be asked to guess which group the participant was allocated to.

At the baseline assessment, demographic and injury details will be recorded. Classification of fracture severity (severe or not severe) will be based on the number of malleoli fractured [20] and the presence of dislocation: bi- or tri-malleolar fractures and any fractures with dislocation will be classified as severe. The assessor will classify fracture severity by examining the radiology entries in the hospital records or, if these are not available, by examining plain radiographs taken before and after the fracture reduction. Two psychological scales will also be used: depression, anxiety and stress will be measured using the Depression, Anxiety, Stress Scales 21-item [24], and pain catastrophising will be assessed using the Pain Catastrophising Scale [25].

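### The seven listed candidate predictors include neither treatment allocation nor baseline LEFS, so if rehabilitation has an effect, pooled predictions are off by half of it in each arm

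*Protocol article*

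**What the plan says.** The Background section of the protocol article gives the aim: "A secondary aim is to identify predictors of outcome after ankle fracture". It motivates the aim by earlier work in which the independent predictors "explained only 9 to 12% of the variance in activity limitation in the short- to medium-term".

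The last paragraph of Statistical analysis says that "univariate linear regression will be used to examine the relationship between seven baseline variables" and "activity limitation at 1-month and 6 months after removal of immobilisation". It names the candidates as "seven baseline variables (fracture severity, pain, ankle range of motion, mobility, depression, anxiety and stress, and pain catastrophising". The next sentence says "A multivariate linear prediction model will be developed" and gives the method by citation. It names no further candidates and no allocation term. Nothing in the paragraph restricts the analysis to one arm or runs it separately by arm.

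Activity limitation is measured with the LEFS, which is a primary outcome. Under Outcome assessment, "Outcomes will be assessed at baseline and 1, 3 and 6 months later", so a baseline LEFS score is planned for every participant. Where the same Statistical analysis section uses group membership in a model, for the treatment comparison and the two effect-modifier analyses, it says so explicitly.

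**The concern.** Participants come from two arms of about equal size that receive different care after immobilisation. If that care changes the outcome, a model without an allocation term estimates one intercept midway between the arms. Its predictions are then too low on average in one arm and too high in the other, and the between-arm difference is counted as residual noise.

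The baseline value of the outcome is a natural candidate predictor and is already collected. Without it, the analysis also cannot show whether the psychological scales predict later limitation beyond the limitation already present at baseline.

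At stake are the calibration and precision of a secondary analysis whose stated motive is that current prediction is imprecise.

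**Working it through.** **Inputs from the article**
- Sample size section: LEFS difference to detect 10 points, SD 15, 80% power, alpha 0.05 (taken as two-sided), 5% loss, total 342.
- Background: earlier predictors explained 9-12% of variance.
- Statistical analysis: seven candidates, with no allocation and no baseline LEFS.
- Not given: the correlation of baseline with follow-up LEFS, or an expected effect at 1 or 6 months.

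**The plan's own figure.** The article states no figure for the prediction model, so the check is on the inputs it lends. A 10-point difference with SD 15 needs 36 per arm. 36/0.95 = 37.9, so 38 per arm and 76 in total. The inflation factor is 2 + 0.5 + 1/0.5 = 4.5, and 76 × 4.5 = 342, as planned. (The printed multiplicand of 72 would give 324 and appears to be a misprint for 76. It has no bearing on this point.) After 5% loss, 342 × 0.95 ≈ 325 remain.

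**Leaving out allocation.** With 1:1 arms and effect D, a pooled prediction is off by D/2 in each arm, in opposite directions. The variance left in the residual is (D/2)². Against a within-arm variance of 15² = 225:

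| D (points) | Error per arm | (D/2)² | Share of total variance | Slope SE ratio, no other predictors |
|---|---|---|---|---|
| 0 | 0 | 0 | 0% | 1.000 |
| 5 | 2.5 | 6.25 | 6.25/231.25 = 2.7% | √(231.25/225) = 1.014 |
| 10 | 5 | 25 | 25/250 = 10% | √(250/225) = 1.054 |

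If the other predictors explain 9% or 12% of the within-arm variance, the residual variance is 225 × 0.91 = 204.75 or 225 × 0.88 = 198. At D = 10 the SE ratios become √(229.75/204.75) = 1.059 and √(223/198) = 1.061. At D = 5 they are 1.015 and 1.016.

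**Are the other slopes biased?** Allocation is randomised and so independent of the baseline variables in expectation. In 4,000 simulated trials (n = 325, D = 10, one predictor explaining 10% of within-arm variance, true slope 4.74), the mean slope was 4.76 without allocation and 4.75 with it. The SDs of the slope were 0.849 and 0.799, a ratio of 1.06. There is no bias, and the loss of precision matches the formula.

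**Leaving out baseline LEFS.** With partial correlation r given the other predictors, residual variance falls by r² when it is added. Without it, slope SEs are larger by 1/√(1 − r²), ignoring collinearity. The values of r are assumptions.

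| Assumed r | Residual variance saved | SE ratio without it |
|---|---|---|
| 0.2 | 4% | 1.02 |
| 0.3 | 9% | 1.05 |
| 0.4 | 16% | 1.09 |
| 0.5 | 25% | 1.15 |

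**The case against.** The strongest reply is that pooling is partly inferred. The seven variables are tied to the univariate step. The multivariable model is given by a cited method, and the article does not say that it is confined to those seven or that allocation and baseline LEFS are excluded. A fuller document might say otherwise. This stands for the multivariable model. It does not remove the point: a regression on one predictor has no allocation term by definition, the list is counted and itemised, and the section names group membership wherever else it uses it. The article does not define mobility, but the sentence uses a different term for the LEFS outcome, so the two are most naturally read as different measures.

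A reader might infer that the predictions would suit neither care pathway, or that a known determinant has been left out. The article does not support either. It describes the effects of rehabilitation as still unclear and reports a previous trial with no overall benefit from an exercise program. The 10 points are a difference to be detected, not an expected effect, and no effect is given for 1 or 6 months. The error is therefore conditional on a non-zero effect and, absent an interaction, is only a shift of the intercept.

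It is also fair that the aim is to identify predictors, that the slopes are unbiased, and that a 5-6% change in standard errors with about 325 participants is unlikely to alter which predictors emerge. That holds, and it keeps the point small. One qualification is that fracture severity is both a listed predictor and a postulated effect modifier. If that interaction exists, its pooled coefficient averages two arm-specific slopes. The interaction is tested elsewhere in the plan, but not within the prediction model as described.

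Finally, the case for baseline LEFS rests on an assumed correlation, and it may overlap with pain, range of motion and mobility. This stands, and is why only a range is given.

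**Conclusion.** The point holds as a minor one. The stated candidate list omits two variables that will be available for everyone, and no allocation term is stated for the prediction analysis.

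For allocation, the size runs from nothing at zero effect to 5 points of miscalibration per arm at the design difference. There, allocation would carry 10% of total variance, about as much as the earlier predictors explained. This assumes equal arms, SD 15 and a multivariable model built from the seven variables on pooled data. The figures for baseline LEFS are illustrative only.

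The point bears on calibration and precision under a secondary aim. It does not touch the treatment comparison, the effect-modifier analyses, the economic evaluation or the sample size.

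**What to change.** State before analysis that:
- allocation is a forced term in the multivariable prediction models at 1 and 6 months;
- each single-predictor regression is adjusted for allocation (and so is no longer described as univariate);
- baseline LEFS is added to the candidate predictors;
- predictions are reported separately for advice and rehabilitation.

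The cost is two degrees of freedom in about 325 participants and a sentence or two of text. No new data are needed. Fixing this in advance also avoids a data-driven choice later. If a fuller document already specifies these terms, it is enough to say so.
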